#### Randomisation and blinding

Immediately after parents submit their baseline assessment online, the trial website is programmed to run a stratified random allocation sequence (based on parent gender) to allocate parent-child dyads to either the control or intervention group.

As such, allocation is concealed from both participants and researchers prior to assignment and baseline assessment. The ‘people administering the treatment’ (for both intervention and control groups) are also masked from the assignment as the intervention is delivered online by an automated trial website. Child informants of the outcomes of interest are assumed to be blinded because they are not direct recipients of the intervention (i.e. parenting program).

### Interventions

#### Intervention group

The ‘Parenting Resilient Kids’ intervention comprises:An individually-tailored feedback report that highlights areas of strength in parenting (i.e., concordant with the Guidelines) and areas for improvement (i.e., not concordant with the Guidelines),An interactive online parenting intervention (up to 12 modules) to support parents in making changes to the identified areas for improvement. Module recommendations are based on responses to the baseline parenting scale.

Feedback reports will be available online immediately after the baseline assessment is completed. Parents will also be emailed a copy of their feedback report and the Guidelines. Five days later, parents will be emailed a link to access their individually-tailored interactive parenting program. Parents can further tailor their parenting program by deselecting recommended modules and/or selecting additional modules. Parents then confirm their selection and can commence their personalised program. The 12 modules comprising the intervention are derived from topics covered in the Guidelines. Modules include illustrations, vignettes, interactive activities, goal-setting exercises, and an end-of-module quiz with immediate feedback to consolidate learning. Module topics and rationale for inclusion are shown in Table 1.

The website is programmed to unlock one module per week from each parent’s program, until all modules in their personalised program have been unlocked irrespective of whether parent has completed preceding modules. Each module will take 15–25 min to complete. Once parents have completed all the modules in their personalised program, they have ongoing access to all 12 modules for the duration of the RCT (up to 4 years).

#### Control group

Parents in the control group are provided with a standardised package of educational materials about child development and wellbeing via the trial website (see Table 2). Parent participants receive an email each week, which provides a link to the corresponding webpage with their information factsheet for that week, for 8 weeks (to match the expected mean number of modules received by the intervention group). This package provides general information to parents as opposed to tailored, actionable strategies, and is designed to represent a selection of resources that are available to parents as part of the current health promotion approach for child wellbeing. The materials are adapted from credible existing resources provided on the Raising Children Network website (www.raisingchildren.net.au).

**Table 2 Tab2:** Factsheet topics and order of presentation

Order of presentation	Topic	Synopsis
Factsheet 1	Child development in the pre-teen years: an overview	Helps parents understand their child’s physical, emotional and social changes in the pre-teen years.
Factsheet 2	Behavioural changes in the pre-teen years	Helps parents understand common behavioural concerns in the pre-teen years and learn ways to encourage good behaviour
Factsheet 3	Connecting and communicating	Helps parents understand the importance of staying connected with their child and provide ideas on ways to improve communication with their child
Factsheet 4	Internet safety	Provides parents with ideas on how to help their child use the Internet safely and responsibly
Factsheet 5	Health and wellbeing in the pre-teen years	Helps parents understand the importance for their child to have healthy lifestyle habits
Factsheet 6	Nutrition during the pre-teen years	Provides parents with ideas on making healthy food choices for their child
Factsheet 7	School and education in the pre-teen years	Helps parent understand how they can support their child’s learning and education
Factsheet 8	Building a strong positive relationship with the school	Provides parent with ideas on how to be involved in their child’s school and to build a positive relationship with the school

### Outcome measures

The following primary outcomes were measured: changes in parental concordance with the Guidelines and changes in child anxiety and depressive symptoms. The secondary outcomes measured were child report of parenting, parent report of general family functioning, and child and parent health-related quality of life.

#### Primary outcome measures

Change in parental concordance with the Guidelines ‘How to reduce your child’s risk of depression and clinical anxiety: strategies for parents of primary school-aged children’ will be assessed by a parenting scale developed for use in this study. The scale consists of 83 questions, and is a criterion-referenced measure assessing parents’ current parenting practices (key parenting risk and protective factors) against specific recommendations in the Guidelines.

The 25-item Revised Children’s Anxiety and Depression Scale (RCADS) [24] will be administered to both parents (parent-report form) and child (child-report form) participants aged 8 to 11 inclusive. Change in child anxiety symptoms, as measured by the 15-item Total Anxiety subscale score, and child depressive symptoms, as measured by the 10-item Depression subscale score, will be tracked.

#### Secondary outcome measures

Child’s report of parenting is assessed by the 10-item Acceptance/Rejection subscale in the latest revision of Schaefer’s Children’s Report of Parent Behaviour Inventory (CRPBI-30, [25] and the 8-item Psychological Control Scale-Youth Self-Report (PCS-YSR) [26]. Each of these scales assesses some aspects of parenting covered in the parenting scale and will be used as a complementary measure for assessing parenting, as well as to form part of the validation of the newly developed parenting scale. This measure is completed only by child participants in Grades 5 and 6 (aged approximately 10–11), to ensure that children are able to provide valid reports on these measures. On these parenting measures, child participants are asked to report on their participating parent only. Parent participants will also complete the parent versions of the CRPBI and PCS-YSR.

General family functioning will be measured by parents’ reports on the 12-item General Functioning subscale of the McMaster Family Assessment Device [27]. Parents’ health-related quality of life will be measured by the 35-item Assessment of Quality of Life (AQoL-8D). The dimensions included in AQoL-8D are: independent living, pain, senses, mental health, happiness, coping, relationships and self-worth [28].

Child’s health-related quality of Life will be measured by Child Health Utility 9D (CHU-9D) and KIDSCREEN-27. The 9-item CHU-9D [29] assesses children’s self-report functioning across nine domains (worry, sadness, pain, tiredness, annoyance, school, sleep, daily routine and activities). The KIDSCREEN-27 [30] developed for children 8–18 years old, and has both self-report and parent proxy versions. It contains 27 items in five domains: physical well-being (five items), psychological well-being (seven items), autonomy and parents (seven items), peers and social support (four items), and school environment (four items). The CHU-9D will be completed by the child participant.

As part of program evaluation, parents in both groups will also be asked six to eight questions relating to the program they have received at each of the follow-up assessments.

#### Protocols for adverse events

Children who express distress during any of the child assessment calls will be contacted by either one of the project managers ([name] or [name]) or the chief investigator ([name]), all of whom are either provisional or registered psychologists. They will assess the level of acute risk and refer parent and child to appropriate follow-up options as required. Parents are provided contact details for the researchers and are encouraged to communicate any concerns about their participation in the program. A T-score of 70 or more on the Revised Children’s Anxiety and Depression Scale (RCADS) is used in the current study for detecting elevated child symptoms [24]. If both child and parent report elevated child symptoms, the project managers ([name] and [name]) will follow-up with the parent participants, to encourage them to discuss these concerns with their child, as well as to provide information about the services they may wish to use if required. Participants are free to withdraw from the research or request that their data be withdrawn at any time.

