#### Inclusion criteria

Parent participants: Parents or guardians of at least one child aged 8 to 11 years (inclusive), who reside in Australia, are fluent in English, have regular access to the Internet and an email account are eligible for the study. Parents are able to participate even if their child opts out. Child participants: children of participating parents/guardians, aged 8 to 11 (inclusive), who reside in Australia, are fluent in English, will be included in the study. The child’s parent or guardian must have provided consent for their child’s participation, and the child must provide informed verbal assent to participate. Only one parent and one child per family are able to participate in the trial.

There are no exclusion criteria in relation to the child participant’s mental health status. While the Guidelines and the intervention are targeted at parents of children aged 5–11 years, the age range of the study sample is restricted to children aged 8–11 years in part due to the availability of psychometrically sound child-report measures that also have parent-informant reports; and in part, to limit the heterogeneity of the sample given the vast developmental differences between children aged 5 and children aged 11.

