### Procedure

A flowchart outlining the study procedures is shown in Fig. 1. Interested parents will be directed to the trial website to review the Explanatory Statements (Parent and Child). Specifically, participants will be informed of the following: (1) study inclusion and exclusion criteria; (2) the two arms of the trial and their chance of being assigned to one of the arms; (3) the potential risks and benefits of participation; (4) privacy and confidentiality arrangements; (5) that the check-in calls provide them with an opportunity to ask any questions related to the study procedures, but will not provide any therapeutic support; and (6) contact helplines should they require immediate professional help. Parents who would like to proceed to participate in the study with their child will be asked to submit their informed consent and contact details on the trial website. One of the project managers ([name] or [name]) will first screen registrations for eligibility. Subsequently, a member of the research team will contact the child participant at a pre-arranged time to obtain verbal assent, and then guide him or her through the online assessment over the phone as required. To assist child participants with literacy issues, the website provides audio clips which dictate the assessment instructions and items to participants when clicked.

Following submission of the child baseline assessment, an automated email will be sent to the parent containing the link to their online baseline assessment. Upon completing their baseline assessment, parents allocated to the intervention group will receive their tailored feedback report, a copy of the Guidelines, and the online parenting program comprising the recommended modules (out of a possible 12). Parents allocated to the control group will receive the first of their eight weekly factsheets.

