Parents in the intervention group will receive a 5-min, weekly phone call from a researcher, starting 7 days after completing their baseline assessment and receiving their personalised feedback report, and every week thereafter for at least 8 weeks. The total number of calls will match the total number of modules selected plus one, with the first call focusing on the feedback report and supporting parents’ familiarisation with their online modules. Research staff will be trained to make these calls following a standard script and will not provide individual advice or therapy. The aims of these calls are to enhance parental engagement and ensure that parents progress smoothly through their allocated program until completion. Parents in the control group will receive a 5-min, weekly phone call from a researcher, starting 7 days after completing their baseline scale, and every week thereafter for 8 weeks to match the number of factsheets received.

At post-intervention (3-month) and each of the follow-up assessments (12-month and 24-month), children and parents will complete the same set of measures using the same procedure as the baseline assessment. Participants can opt out at any stage of the study. Verbal assent will be obtained from the child prior to asking them to complete each follow-up assessment.

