#### Confidentiality

Information obtained from the research will only be accessible by the researchers, and all electronic files will be password protected. Reports arising from the research will only include group data, and individual participants will not be identifiable in any way. As discussed in the adverse events protocol above, if both child and parent reported anxiety or depression scores on the RCADS are elevated, only the participating parent will be informed via email. However, no individual data will be provided to the parent. All data will be securely destroyed after a minimum of 5 years from when the final report of the study is published.

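### The RCADS alert needs both an elevated child and an elevated parent report, so it cannot fire at a follow-up visit where only the parent reports

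*Protocol article*

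**What the plan says.** Under *Protocols for adverse events*, the protocol article sets an RCADS T-score of 70 or more as the mark of elevated child symptoms. The action is tied to two informants: "If both child and parent report elevated child symptoms, the project managers" follow up with the parent, "to encourage them to discuss these concerns with their child, as well as to provide information about the services they may wish to use". The *Confidentiality* section repeats the condition: "if both child and parent reported anxiety or depression scores on the RCADS are elevated, only the participating parent will be informed via email", without individual data. Neither section says what happens when only one of the two forms is available.

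Two other sections make that situation possible. *Inclusion criteria*: "Parents are able to participate even if their child opts out". *Procedure*: participants may leave at any stage, and "Verbal assent will be obtained from the child prior to asking them to complete each follow-up assessment".

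There is a second safety route that does not depend on a score: "Children who express distress during any of the child assessment calls will be contacted by either one of the project managers" or the chief investigator, who assess acute risk. Parents also hold the researchers' contact details and are told of helplines before they consent.

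**The concern.** A rule that needs two elevated reports is a defensible choice when both informants have answered: a child report below 70 is evidence against the parent's report. A missing child report is no evidence either way, yet under the stated rule it has the same effect as a reassuring one, and no contact follows.

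The trial places no limit on the child's mental health at entry, so some children will have high scores. If the child has stopped taking part and the parent then reports symptoms at or above the trial's own threshold, the plan gives staff no score-based reason to act. The remaining routes depend on the parent taking the initiative, or on a call with the child taking place.

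What is at stake is a modest participant-safety step. No treatment effect, standard error, power or type I error rate depends on it.

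**Working it through.** **1. The rule set against the participation terms**

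The stated trigger is (child T ≥ 70) AND (parent T ≥ 70).

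| Child RCADS | Parent RCADS | Condition met? | Score-based contact |
|---|---|---|---|
| ≥ 70 | ≥ 70 | yes | yes |
| < 70 | ≥ 70 | no | none (contrary evidence exists) |
| missing | ≥ 70 | cannot be met | none (no contrary evidence) |

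The third row can occur at 3, 12 and 24 months, because a parent may continue without the child and assent is asked afresh each time. Baseline is left out: *Procedure* sends the parent the baseline link only after the child's baseline form is submitted.

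**2. Does the distress route cover the third row?**

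Only in part. At baseline "a member of the research team will contact the child participant at a pre-arranged time to obtain verbal assent", and at follow-up "children and parents will complete the same set of measures using the same procedure as the baseline assessment". A child who declines on such a call has still spoken to a researcher, so visible distress could be picked up. Where no call with the child takes place, that route is absent.

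**3. How many reports might be affected?**

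The article gives neither a rate of parent-only visits nor a T-score distribution, so this is an illustration.

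Inputs:
- From *Sample size*: 340 dyads, attrition 10–15%. Assumed to apply at each wave.
- Assumed: 5–15% of the remaining dyads have a parent form only.
- Assumed: parent T-scores are normal with SD 10 and mean 50, or mean 55 (half an SD higher).
- Assumed: Total Anxiety and Depression scores correlate at 0.8 to 0.5, and either one at 70 or more counts as elevated.

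Dyads remaining: 340 × 0.85 = 289; 340 × 0.90 = 306.

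Parent-only visits per wave: 289 × 0.05 = 14.45; 306 × 0.15 = 45.9.

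Probability that at least one subscale is elevated = 2 × P(Z ≥ z) − P(both ≥ z), with the joint term from the bivariate normal distribution (results rounded after calculation):

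| Mean | z | P(Z ≥ z) | r | P(both) | P(either) |
|---|---|---|---|---|---|
| 50 | 2.0 | 0.0228 | 0.8 | 0.0098 | 0.0357 |
| 50 | 2.0 | 0.0228 | 0.5 | 0.0041 | 0.0414 |
| 55 | 1.5 | 0.0668 | 0.8 | 0.0349 | 0.0988 |
| 55 | 1.5 | 0.0668 | 0.5 | 0.0183 | 0.1153 |

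Elevated parent-only reports per wave:
- Mean 50: 14.45 × 0.0357 = 0.5 to 45.9 × 0.0414 = 1.9.
- Mean 55: 14.45 × 0.0988 = 1.4 to 45.9 × 0.1153 = 5.3.

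These are visits, not children. Over three waves, the number of distinct children lies between one wave's count (the same children each time) and three times that count (different children each time):
- Mean 50: 0.5 to 3 × 1.9 = 5.7.
- Mean 55: 1.4 to 3 × 5.3 = 15.9.

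**The case against.** - **The article is a condensed account.** What staff do when a form is missing could sit in a fuller distress procedure, and the text promises action when both reports are elevated without forbidding it otherwise. It is true that no prohibition is written. But the trigger is stated twice with the same joint condition, and *Confidentiality* ties informing the parent to it. The point concerns a stated rule that does not fit the stated participation terms, rather than an omitted detail.

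- **Visit order.** Follow-up uses the baseline procedure, in which the child's form comes first, so parent-only follow-ups may be uncommon. This bears on frequency. It does not rule such visits out, because the parent may continue after the child opts out.

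- **Little is lost.** The parent is the one reporting the symptoms, has helplines and contact details, and in the intervention arm has the Guidelines, which cover help seeking. Most of this stands, and it is why the point is minor. Yet in the two-informant case the parent has also reported the symptoms, and the plan still makes the contact. Nothing in the article says the parent is otherwise told that their answers reach the threshold.

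- **The size is mostly assumed.** Correct. Only the attrition figure and the 340 dyads come from the document, and the range from 0.5 to 15.9 children is too wide to show that the gap is material.

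- **The change costs more than a sentence.** Participants are told the confidentiality arrangements before consent, and 321 of 340 dyads had already been recruited. An ethics amendment, and perhaps revised participant information, may be needed. Acting on one uncorroborated report is also a matter of judgement. Both points stand as costs.

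**Conclusion.** The concern holds as a minor one, worth considering. As written, a follow-up visit with a parent RCADS and no child RCADS cannot meet the alert condition, whatever the parent's score. That conclusion rests on the text alone. Its frequency is unknown; under the assumptions listed, it is roughly 0.5–1.9 elevated parent reports per wave with mean 50, or 1.4–5.3 with mean 55. The consequence is a missed prompt and missed service information. Acute-risk assessment runs through the separate distress route, which is lacking only where there is no call with the child. The two-informant rule is not in question where both informants report.

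**What to change.** Change two places in the protocol.

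- *Protocols for adverse events*, add a sentence along these lines: *If a visit has no child RCADS, a parent-report T-score of at least 70 on Total Anxiety or Depression is sufficient on its own, and the project managers email the parent the same advice and service information, giving no individual scores.*
- *Confidentiality*, extend the condition with a clause: *or the parent-reported score is elevated and that visit has no child RCADS.*

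Keep the two-informant rule wherever both forms are present.

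The cost is one sentence, one clause and one extra alert condition, using parent scores already collected, plus a possible minor ethics amendment. The downside is a few additional emails per wave (about 1–2 with mean 50, up to about 5 with mean 55). Some will go to parents who already know of the problem, and each rests on a single report.

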#### Training for fidelity

Research staff are trained to conduct the weekly check-in calls with parents using a standard script (i.e. standard list of questions and prompts). At least one project manager ([name] or [name]) will oversee the daily operation of the trial, and two research assistants will conduct the phone calls to parent and child participants. Extensive efforts will be made to minimise non-response and drop-out rates, including reminder calls, text messages, emails, participant reimbursement, and child birthday cards.

#### Confidentiality

Information obtained from the research will only be accessible by the researchers, and all electronic files will be password protected. Reports arising from the research will only include group data, and individual participants will not be identifiable in any way. As discussed in the adverse events protocol above, if both child and parent reported anxiety or depression scores on the RCADS are elevated, only the participating parent will be informed via email. However, no individual data will be provided to the parent. All data will be securely destroyed after a minimum of 5 years from when the final report of the study is published.

